#### (7) Adverse events

Adverse Events (AE) during or ≤1h after session, including headache, scalp dysesthesia/paresthesia at stimulation site, muscle pain of temporal or neck muscles and seizures, will be documented after each treatment session and during the whole treatment period.

### 4. Statistical analyses

The data of MoCA-BJ, TMT, MBI, LIADL and SS-QOL were shown as mean ± standard deviation (SD) and analyzed by the range analysis and one-way analysis of variance (ANOVA), which was used the SPSS 22.0 software (IBM, Armonk, NY, USA, 2020). The range analysis was used to determine the influence of each parameter at a specific level on the effect indicator and obtain the optimum combination of rTMS parameters. The one-way ANOVA was used to determine the statistical significance in nine different parameters’ combination of rTMS. P < 0.05 was considered significant.

For ALFF and FC maps, paired T-test will be used for intra-group comparison and one-way ANOVA analysis will be used for inter-group comparison in the three stimulating site subgroups. Then multiple comparison correction will be performed using Gaussian random field theory (GRF) with voxel *p* < 0.005, cluster *p* < 0.05. The Pearson correlation analyses were used to calculate the correlations between the changes in ALFF and FC with the clinical symptom scores at baseline and the end of the rTMS treatment (*p* < 0.05).

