#### (4) Sample size

Because no previous orthogonally designed study provides a significant difference of MoCA or MMSE scores for rTMS treatment to PSCI, which would allow us to accurately estimate the adequate sample size for this trial, we decided to recruit 45 PSCI patients who will be randomly divided into nine groups and three subgroups based on orthogonal design (5 patients per group, 15 patients per stimulating site subgroup), in consideration of the research grant, the recruitment feasibility and the recommended sample size in neuroimaging research (medians:14.5) [17].

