### 3. Outcomes

The primary outcomes are the Montreal Cognitive Assessment Beijing Version (MoCA-BJ) and the Trail-Making Test (TMT). The secondary outcomes are the modified Barthel index (MBI), the Lawton Instrumental Activities of Daily Living Scale (LIADL), the stroke-specific quality of life (SS-QOL), the functional magnetic resonance imaging (fMRI) scan and the adverse events. All measurements of clinical assessments were administered three times: pre-treatment (baseline), post-treatment, and at a three-month follow-up. All of the cognitive assessments were performed by a trained neuropsychologist who was blind to the treatment status of the participants throughout the study. The MRI scan were conducted at baseline and at the end of rTMS treatment.

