#### (2) TMT

The trail marking test (TMT) was firstly used in 1944 for America army individual intelligence assessment [22]. Nowadays, it is widely employed as a diagnostic tool for visual attention and executive functioning and the processing speed for neuropsychological diseases [23, 24]. It consists of two parts in which the subject is instructed to connect a set of 25 circles containing numbers (Part A) or numbers and letters (Part B) arrayed pseudorandomly on a letter-size sheet of paper as fast as possible while still maintaining accuracy.

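### The Trail-Making Test, a primary outcome that appears to be a completion time, is analysed without a scale suited to skewed times and without the baseline value, which costs power

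*Protocol article*

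**What the plan says.** All references are to the protocol article.

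- Section 3, Outcomes: "The primary outcomes are the Montreal Cognitive Assessment Beijing Version (MoCA-BJ) and the Trail-Making Test (TMT"). Clinical assessments are made before treatment, after treatment and at three months, so a baseline TMT exists for each patient assessed.
- Section 3 (2), TMT: patients connect the circles "as fast as possible while still maintaining accuracy". No score or unit is given, but a completion time is the natural reading.
- Section 4, Statistical analyses: "The data of MoCA-BJ, TMT, MBI, LIADL and SS-QOL were shown as mean ± standard deviation (SD"), and the same sentence has all five measures "analyzed by the range analysis and one-way analysis of variance (ANOVA"). The range analysis is to "obtain the optimum combination of rTMS parameters". On the test: "The one-way ANOVA was used to determine the statistical significance in nine different parameters’ combination of rTMS". On the threshold: "P < 0.05 was considered significant".
- Section 1 (4), Sample size: "5 patients per group, 15 patients per stimulating site subgroup". No power calculation is given.

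The section names no transformation and no covariate for TMT.

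**The concern.** A completion time has a floor and commonly a long right tail, and these patients are selected for cognitive impairment (MoCA of 24 or less). Group means of 5 and level means of 15 on such a scale are noisy, and the within-group variance that forms the ANOVA denominator is inflated by the tail. The trial also measures each patient's TMT before treatment. That value should explain much of the variation between patients, yet a one-way ANOVA on treatment group does not adjust for it.

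At stake is the efficiency of the analysis of a primary outcome in a trial of 45 patients, where power is already scarce. To a lesser degree, the combination named as optimal may depend on the scale on which TMT is averaged.

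This objects to a stated choice. The article names the summary, both methods and the significance level for TMT.

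**Working it through.** **Inputs from the article.** Nine groups of 5 give 9 × 5 = 45. Each level of each factor appears in three groups, so 3 × 5 = 15 per level, which matches the stated 15 per site. Table 2 is orthogonal. The group list printed below it gives different combinations for several groups, and the two must be reconciled. The list is also orthogonal with 15 per level, so nothing here depends on which is used. There is no stated power figure to reproduce.

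**Assumptions, not in the documents.** TMT is scored as uncapped time. Times are log-normal with log-SD s = 0.5 or 0.6. One site is truly 25% or 35% faster, and the other factors have no effect. Post-treatment values are compared.

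**Step 1: the planned ANOVA on log times.** Let d = ln(1 − reduction). Three groups lie at 2d/3 from the overall mean and six at −d/3, so the squared deviations sum to 3(4/9)d² + 6(1/9)d² = 2d². With 5 per group the noncentrality is 5 × 2d²/s² = 10d²/s², on 8 and 36 degrees of freedom. For 35% faster, d² = (ln 0.65)² = 0.1856; for 25% faster, d² = (ln 0.75)² = 0.0828.

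**Step 2: the same test on raw times.** This has no simple formula and was simulated on the Table 2 array, with 20,000 or more trials per setting.

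| Site faster by | Log-SD | 10d²/s² | Power, log | Power, raw |
|---|---|---|---|---|
| 35% | 0.5 | 7.42 | 36% (simulated 36-37%) | 25% |
| 35% | 0.6 | 5.15 | 25% | 16% |
| 25% | 0.5 | 3.31 | 17% | 13% |
| 25% | 0.6 | 2.30 | 13% | 9% |

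With no true effect, the raw-time ANOVA rejects in 4.1% to 4.8% of trials for log-SD from 0.3 to 0.9.

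**Step 3: what the range analysis selects.** Correct site chosen, raw against log:

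| Site faster by | Log-SD | Raw | Log | Gain (points) |
|---|---|---|---|---|
| 35% | 0.5 | 97.7% | 98.5% | 0.8 |
| 35% | 0.6 | 94.0% | 95.7% | 1.7 |
| 25% | 0.5 | 88.4% | 90.0% | 1.6 |
| 25% | 0.6 | 81.6% | 84.4% | 2.8 |

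Raw and log rankings name a different best level for at least one of the four parameters in 47% and 53% of trials with no true effect (log-SD 0.5 and 0.6), and in 43% and 49% with one site 35% faster. Most of this occurs among parameters with no true effect, where either scale is picking noise.

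**Step 4: adding the baseline.** Assume a correlation of r = 0.7 between log baseline and log post-treatment time. The residual variance falls by the factor 1 − r² = 1 − 0.49 = 0.51, so the noncentrality rises by 1/0.51 = 1.96, for one degree of freedom spent (8 and 35). Approximate power becomes:

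- 35% faster: noncentrality 7.42/0.51 = 14.55, power 68% (log-SD 0.5); 5.15/0.51 = 10.11, power 49% (log-SD 0.6).
- 25% faster: 3.31/0.51 = 6.49, power 31%; 2.30/0.51 = 4.51, power 22%.

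That is 1.7 to 1.95 times the power of log alone. These figures ignore the small loss from chance baseline imbalance and are slightly optimistic. In simulation, ranking the adjusted log-scale means picks the correct site in about 94-99% of trials.

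**The case against.** **A stronger reading is tempting:** that a few very slow patients decide the optimum, and that a log scale would prevent it. The arithmetic looks persuasive. One patient at 600 s among peers at 150 s moves a 5-patient mean by (600 − 150)/5 = 90 s and a 15-patient mean by 450/15 = 30 s. The documents do not support that reading. Neither the 600 s patient nor the long tail is in them. The log scale changes correct-site selection by only 1-3 points. Omitting the two slowest of 45 changes the named optimum in about 61% of null trials even when the data are normal, against 77% at log-SD 0.5. Most of the instability therefore comes from ranking 15 per level without a test, which a transformation leaves in place.

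**Power on a main-effects test is not the sponsor's power.** A test of site alone (2 and 36 degrees of freedom) would show 54% raw against 64% log at 35% faster and log-SD 0.5. The article plans a nine-group comparison, where power is low on either scale.

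**The score is not defined.** A time limit would shorten the tail. With an assumed 300 s cap, log-SD 0.5 and one site 30% faster, ANOVA power is 22.0% raw against 25.3% log, compared with 18.2% against 25.2% uncapped. The article also does not say whether post-treatment values or changes are analysed. Changes would use the baseline by subtraction and partly cancel a patient who is slow at both visits. At r = 0.7 on the log scale they leave a relative variance of 2(1 − 0.7) = 0.60, against 0.51 for ANCOVA. These points stand and limit the size of the concern.

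**A transformation may be in an unseen analysis plan.** An ANOVA of log times is still an ANOVA, so the article does not exclude it. But the article commits to mean and SD, and a one-way ANOVA leaves no room for a covariate. Nor does it say that TMT alone, or with MoCA-BJ, names the optimum: the range analysis is applied to all five measures.

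**Conclusion.** The point holds as one of efficiency. The method stated for this primary outcome takes account neither of likely skewness nor of the baseline measurement. Under log-normal times with log-SD 0.5-0.6, moving to the log scale raises the power of the planned ANOVA by about 11 and 9 points for a 35% difference at one site, and by about 4 points for a 25% difference. Baseline adjustment is the larger gain: about double the power of log alone if the baseline correlation is 0.7.

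A reader might infer that the raw-time ANOVA gives false positives, or that the log scale would make the optimum reliable. Neither follows. Type I error stays near nominal, and the choice of optimum remains unstable with 15 per level and no test. The skew, the effect sizes, the correlation and the absence of a time cap are all assumptions. The direction of the gain does not depend on their exact values, but its size does.

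**What to change.** State in section 4 that TMT is analysed as log post-treatment time in an ANCOVA with treatment group and log baseline time, and likewise at three months. Report ratios of geometric means with confidence intervals. Run the range analysis on the baseline-adjusted log-scale level means: for each level, the mean log post-treatment time minus b × (level mean minus overall mean of log baseline), where b is the ANCOVA slope. Describe raw times by median and quartiles instead of mean and SD. Name the TMT score to which this applies, and fix the scale before unblinding, because raw and log rankings often differ.

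The cost is a few lines of analysis text and one residual degree of freedom (35 instead of 36). No new data or patients are needed, since the baseline TMT is already collected. The drawback is that results read as ratios rather than seconds. The change reduces the instability of the named optimum but does not remove it, so the optimum should still be reported with its uncertainty.

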**Discussion:**

This study evaluates the optimum parameters of rTMS for patients with post-stroke cognition impairment and explores the alteration of neural function in DMN, DAN, CEN brain network. These results would facilitate the standardized application of rTMS in cognition impairment rehabilitation.

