## Introduction

Post-stroke cognitive impairment (PSCI) is one of the vascular cognitive impairments and probably develop into dementia [1]. It was reported that 20–70% stroke survivor suffered from the cognitive impairment within 6 months after stroke attack [2, 3]. It is not only a common, important disability after stroke but also could hinder the rehabilitation of stroke-related sequelae including motor dysfunction, sensor deficits and the limited activities of daily living [4]. The pathogenesis of PSCI is multifactorial being similar with VCI. In terms of brain structure, it is generally related to focal, multifocal or diffuse cortical and/or subcortical large infarct, microinfarcts or lacunes, as which is often affected important brain areas (thalamus, frontobasal and/or limbic systems, etc.) [5]. Functionally, the PSCI is due to the disfunction of neuronal metabolism, activation and connectivity, while the exact mechanism between vascular lesion, cognition, and neuroplasticity are not completely understood [6]. Current research shows that many non-invasive neuromodulatory techniques could improve cognitive impairment via neuroplasticity [7]. As a non-invasive brain stimulation,the repetitive transcranial magnetic stimulation (rTMS) was widely used as a primary or an add-on treatment to improve cognitive function in patients with stroke [8]. Several meta-analyses confirmed its promising and positive effect on PSCI [9–11]. In these studies, mostly rTMS schemes included four primary parameters: stimulating site, frequency, intensity and pulse number, however, the rTMS intervention scheme varied substantially and the considerable heterogeneities of rTMS parameters were the great challenging in its clinical practice. Furthermore, although accumulating studies have shown that rTMS could improve the cognitive function in many neurological and psychological diseases [12, 13], the brain functional mechanism is still unclear. The present study hypothesized that rTMS could promote the cognition recovery with an optimal parameter combination and it might be objectively existed that the interaction effects between the four parameters: stimulating site, frequency, intensity and pulse number. Furthermore, we predicted that the mechanism of rTMS might be related with the neuroplasticity in three brain networks: default mode network (DMN), dorsal attention network (DAN), central executive network (CEN). Hence, the prospective, single-center, orthogonally-designed, triple-blind randomized controlled trial will be conducted and will be aimed to explore the rTMS optimum parameters regimen for PSCI based on stimulating site, frequency, intensity and pulse number and the neuroimaging mechanism in default mode network (DMN), dorsal attention network (DAN), central executive network, (CEN) following rTMS treatment in PSCI patients. All participants will be assigned averagely to one of nine paralleled active rTMS groups which are designed according to the L_9_(3^4^) orthogonal array with four different parameters: stimulating site, frequency, intensity and pulse number. This trial protocol will be written in adherence to the standard protocol items: recommendations for interventional trials (SPIRIT) 2013 guidelines [14].

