### 2. Interventions

#### (1) rTMS protocol

The rTMS treatments were delivered by a magnetic simulator (YRD CCY-I, YIRUIDE medical equipment co., LTD, Wuhan, China) with a figure-8 coil. The rTMS protocol was designed as nine combinations of four parameters at three different levels in each parameter: stimulating site (the dorsolateral prefrontal cortex, DLPFC, Brodmann areas 9 and 46; the inferior frontal gyrus, IFG, Brodmann areas 44 and 45; the temporo-parietal cortex, TPC, Brodmann areas 39 and 40), frequency (5Hz, 10Hz, 20Hz), intensity (90%, 100%, 110% of the resting motion threshold, RMT) and pulse number (1000, 1500, 2000), the detailed information are showed in Tables 1 and 2. The aforementioned rTMS parameters and different levels were predetermined based on the previous studies involving in rTMS treatment to cognition impairment duo to various neurological and psychological diseases. Once the PSCI patients were recruited, they were randomly allocated into one of nine active rTMS groups, a total of 20 sessions (four weeks, five consecutive daily sessions and two days of rest per week) active rTMS treatments with different parameters combination will be administered by two therapists with more than 5 work experience at the neuromodulating center of the rehabilitation medicine department, West China Hospital, Sichuan University. In order to improve the patient’s adherence to the intervention protocols, once every rTMS session was completed, a predesigned treatment record card should be filled and signed by the rTMS therapists and the patients or their authorized persons and ultimately returned to the study researchers.

**Table 1 pone.0271283.t001:** The orthogonal experimental factors and levels of rTMS.

Level	Experimental factor			
	A (Site)	B (Frequency, Hz)	C (Intensity, %RMT)	D (Pulse)
1	DLPFC	5	90	1000
2	IFG	10	100	1500
3	TPC	20	110	2000

Note: DLPFC: Dorsolateral prefrontal cortex; IFG: Inferior frontal gyrus; RMT: Resting motor threshold; rTMS: Repetitive transcranial magnetic stimulation; TPC: Temporoparietal cortex

**Table 2 pone.0271283.t002:** The orthogonal array L9(34).

Groups	Site (A)	Frequency (B)	Intensity (C)	Pulse (D)	rTMS protocols	Sample Size
1	TPC	5 Hz	100%RMT	1500	A_3_B_1_C_2_D_2_	5
2	IFG	20 Hz	100%RMT	1000	A_2_B_3_C_2_D_1_	5
3	IFG	10 Hz	90%RMT	1500	A_2_B_2_C_1_D_2_	5
4	TPC	10 Hz	110%RMT	1000	A_3_B_2_C_3_D_1_	5
5	DLPFC	5 Hz	90%RMT	1000	A_1_B_1_C_1_D_1_	5
6	IFG	5 Hz	110%RMT	2000	A_2_B_1_C_3_D_3_	5

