## Discussion

As a non-invasive brain stimulation technique, the rTMS uses high intensity magnetic field pulses to modulate neural activity and in turn modifying the brain function. Over the past few decades, rTMS is widely applied into the cognition impairment due to many neurological, psychiatrical and psychological diseases, such as stroke, Alzheimer’s disease, Parkinson’s disease, schizophrenia, obsessive compulsive disorder. Several meta-analyses and RCT have showed that the safe and beneficial value of rTMS in cognitive function rehabilitation [10, 33–35]. Given the more and more application of this method in clinical and research settings, it is crucial to understand what is the optimal parameters of rTMS for cognition impairment and how the rTMS modulates brain function via the high intensity magnetic field pulses. Fortunately, some researchers have realized these two key points. Beynel L et al. thought that the rTMS parameters include a vast composition of spatial and temporal parameters: coil geometry, stimulation target, stimulation intensity; pulse waveform, pulse train frequency, number of pulses, etc [36]. while it does not be summed precisely from the perspective of clinical application. Based on the previous literature related to multiple sessions of rTMS for cognition impairment, we hold the opinion that the most important four parameters of rTMS are stimulating site, stimulating frequency, stimulating intensity and pulse number. Orthogonal design is a powerful method for comparative effectiveness research, especially for intervention with multiple parameters, it could significantly reduce the experiment numbers and alleviate the research workloads [37]. In rehabilitation medicine, many physical modalities are delivered with a specific equipment by presetting several parameters in the meantime. It is important that these parameters should be investigated at the same time when we are going to assess the efficacy and safety of this intervention. For example, the rTMS will be delivered to a patient with cognition impairment, the stimulating site, frequency, intensity and pulses should be predetermined meanwhile. However, in the previous studies, it was common that only one parameter, such as frequency, be compared with different level, or be compared between active and sham rTMS. It is not entirely and exactly consistent with clinical practice. Hence, in order to investigate the optimum parameters of clinical value of rTMS for post-stroke cognition impairment, the present study is designed orthogonally with L_9_(3^4^) orthogonal array based four parameters with three different level in each parameter (sites: DLPFC, IFG, TPC; frequency: 5Hz, 10Hz, 20Hz; intensity: 90%RMT, 100%RMT, 110%RMT; pulse number: 1000 pulses, 1500 pulses, 2000 pulses). On the other hand, although many studies showed that the modulatory effect of rTMS on brain function, ig. enhancing the neural activity and the connectivity between different brain regions [38], is correlated to the improvement of cognition function [39], the exact neurological mechanism has not been understanded very well. Giacomo Koch et al. showed that the rTMS stimulation on precuneus enhances memory and neural activity and connectivity in default mode network [40]. Recep A Ozdemir et al. Showed that the default mode network (DMN) and the dorsal attention network brain network (DMN/DAN) specificity of rTMS activations is correlated with cognitive performance in healthy volunteers [41]. Reza Kazemi et al. showed that the bilateral rTMS stimulation on DLPFC changes resting state in CEN, DMN brain networks and cognitive function in patients with bipolar depression [42]. However, whether the brain networks related to attention and executive function (CEN, DMN, DAN) is enhanced activity and connectivity and is correlated with the cognitive improvement following the rTMS stimulation in patients with post-stroke cognition impairment are still unclear. Therefor, in the current study, the amplitude of low-frequency fluctuation (ALFF) and the functional connectivity (FC) of the resting-state fMRI signal has been adopted to reflect the regional brain network (CEN, DMN, DAN) activity and connectivity and further our understanding of the complex cognitive function recovery process underlying metaplasticity with rTMS, demonstrate how the adaptive metaplasticity can contribute to the cognition impairment, and show that whether the maladaptive metaplasticity play a role in the cognitive pathophysiology [43].

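### The rule for the optimum regimen can name a combination that no patient received; such a result is a prediction under additivity and should be labelled so

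*Protocol article*

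**What the plan says.** The Introduction assigns patients to "one of nine paralleled active rTMS groups which are designed according to the L_9_(3^4^) orthogonal array", and the rTMS protocol section describes "nine combinations of four parameters at three different levels in each parameter". Under Sample size the split is "5 patients per group, 15 patients per stimulating site subgroup".

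Under Statistical analyses, range analysis is to gauge how each level of each parameter affects the outcome, and from this to "obtain the optimum combination of rTMS parameters". The data that enter it are listed: "The data of MoCA-BJ, TMT, MBI, LIADL and SS-QOL were shown as mean ± standard deviation (SD) and analyzed by the range analysis". A one-way ANOVA then compares the nine arms. Nothing limits the named optimum to those arms, and no step confirms it.

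The Introduction also hypothesises that the four parameters interact. The Discussion part of the Abstract concludes: "These results would facilitate the standardized application of rTMS in cognition impairment rehabilitation".

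**The concern.** Range analysis compares level means one parameter at a time and assembles the winner from four separate choices. In a one-ninth fraction of the full factorial, the assembled combination need not be among those delivered. Its expected response is then an additive extrapolation, and nobody has been observed on it for efficacy or tolerability.

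The plan calls this result the optimum and ties it to standardised clinical use. The ANOVA offers no protection, because it tests differences among the nine delivered arms and says nothing about a combination outside them. The extrapolation holds only if the parameters do not interact, and the article itself expects that they may.

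**Working it through.** **Inputs.** Four parameters at three levels, nine arms of 5 (Introduction, rTMS protocol, Sample size). The plan's own figures reproduce: 9 × 5 = 45 patients, and 45 / 3 = 15 per site. Because the array is orthogonal, there are also 15 per level of every other parameter. The article gives no SD or effect size, so effects below are assumed and expressed in SD units. It does not spell out range analysis either; I take it as choosing the best level mean for each parameter.

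**Undelivered combinations.** 3^4 = 81 can be named and 9 are delivered, leaving 81 − 9 = 72.

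**No parameter matters.** The four choices are independent and each level is equally likely, so P(undelivered) = 72/81 = 89%.

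**With effects.** I simulated arm means with SD 1/√5, additive effects, and the best level mean chosen for each parameter, with 200,000 trials per scenario.

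| Assumed truth | Step per level | Named optimum undelivered | Highest frequency, intensity and pulses all named |
|---|---|---|---|
| No effect | 0 | 89% | 4% |
| Frequency, intensity and pulses all rise; no site effect | 0.25 SD | 92% | 37% |
| Same | 0.5 SD | 97% | 76% |
| Only frequency rises | 0.25 / 0.5 SD | 89% / 89% | 8% / 10% |
| True best is group 9; response falls with each level away from it on all four parameters | 0.25 SD | 75% | 10% |
| Same | 0.5 SD | 35% | 6% |

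Results agree to within 0.01 whether the arms are taken from Table 2 or from the group list. Neither version has an arm at 20 Hz with 110% RMT and 2000 pulses, so in the rising scenarios the true best is off the design by construction.

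**Can additivity be checked?** Nine arms give 9 − 1 = 8 between-arm degrees of freedom. Four three-level parameters use 4 × 2 = 8, which leaves 8 − 8 = 0. The 45 − 9 = 36 within-arm degrees of freedom measure patient variation and carry no information on interaction. Any interaction is mixed into the main effects from which the optimum is chosen.

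**Tolerability.** Both printed arrays contain every pair of levels once for each of the six pairs of parameters. Each pair of levels therefore has 5 patients and each single level 15. An undelivered full combination has none.

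**Which nine arms?** Table 2 and the list beneath it differ for groups 2, 3, 4, 7, 8 and 9. For example, group 2 has 100% RMT and 1000 pulses in the table but 90% RMT and 1500 pulses in the list. They share three combinations, so together they cover 9 + 9 − 3 = 15. Even if all 15 counted as delivered, 66/81 = 81% would remain undelivered. In group 1 of the list, the trains give 5 × 10 × 20 = 1000 pulses against the stated 1500.

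**The case against.** Predicting untested cells from level means is what a fractional orthogonal array is for, and the Discussion states the trade-off openly: fewer experiments. The Introduction speaks of exploring. The limitations concede the small sample and the simple level design, and point to a larger study. This stands as a defence of the design. It does not cover the label, because an additive prediction needs additivity, which the article doubts and cannot test. The limitations do not say that the optimum may never have been given.

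Three stronger readings are tempting and are not supported.

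- A reader might infer that the Discussion promises a joint judgement of efficacy and safety, which an efficacy-only rule then breaks. The sentence containing "when we are going to assess the efficacy and safety of this intervention" says that the four parameters should be studied together. It does not say that safety enters the choice of optimum.
- A reader might infer that there would be no tolerability data at all. Adverse events are a secondary outcome recorded after every session, and each level and each pair of levels is observed. Only the full combination is not. Tabulating adverse events by level is ordinary content for an analysis plan that is not shown, so its absence here is no fault.
- A reader might take 89% to 97% as the general size. No section of the article supports a steady rise in all three dose parameters, and the share falls well below half if a delivered arm is truly best and effects are large.

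**Conclusion.** The point holds as one about labelling and inference. As written, the rule can name a combination outside the nine arms and call it the optimum. The chance is 89% if nothing matters, 92% to 97% under the rising scenarios, and about 75% down to 35% if the true best is a delivered arm. These figures assume additive effects, 5 patients per arm with complete data, normal errors, and range analysis in its usual sense.

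An undelivered optimum would rest on an absence of interaction that the article's own hypothesis questions and its saturated array cannot examine. The nine-arm ANOVA cannot support it. The article shows neither a broken promise on safety nor a lack of adverse-event data in general. The change is worth making because it alters what the trial may conclude and costs little.

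**What to change.** 1. Reconcile Table 2 with the group list, and group 1's train settings with its stated pulse number, so that the nine delivered combinations are known. Which version is right is for the investigators to state.
2. Under Statistical analyses, call the range-analysis result a predicted combination under additivity, and state whether it is one of the nine delivered arms.
3. If it is not, report beside it the best delivered arm with its own mean, interval and adverse events. Limit the conclusion to a combination that is predicted, not tested, and in need of confirmation.
4. Qualify the closing claim of the Abstract in the same way.

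Showing adverse events by level of each parameter next to the range analysis would help, but is optional.

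The cost is a few sentences and one comparison from data already collected, with no change to arms or sample size. The conclusion becomes somewhat weaker. The best delivered arm has only 5 patients, so its 95% interval would be about ± 2.03/√5 = ± 0.91 SD (pooled SD on 36 degrees of freedom). Its mean is also flattered by having been picked as the best of nine, which the report should say.
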